### Participating centres

More than thirty-five teaching hospitals in the Netherlands are participating in this trial, including six academic centres.

### Study population

This study consists of patients eligible for surgical treatment of perforated diverticulitis. Inclusion criteria are age between 18 and 85 years, a clinical suspicion for perforated diverticulitis and free gas on plain abdominal radiography, free gas on CT, or peritonitis with diffuse fluid or gas on CT.

### Ethics

This study will be conducted in accordance with the principles of the Declaration of Helsinki and Good Clinical Practice guidelines. Medical ethics approval has been obtained by the medical ethics committee from the Academic Medical Centre in Amsterdam, dated September 30th, 2009. Prior to randomisation, written informed consent must be obtained from all patients.

### Study outline

Diagnostic laparoscopy: a careful inspection of the stomach, duodenum and sigmoid is performed to localise the site of perforation. In case of peritonitis due to a perforated diverticulum it must be attempted gently to locate the site of perforation. Careful removal of adherent omentum or bowel is tried. If clearly adherent, it should be left in place.

If no obvious perforation is apparent and faecal content is absent, the patient is randomised online between treatment with LL, HP or PA in a ratio 2:1:1.

In case of an overt perforation or intra-abdominal contamination with faeces, the patient is not eligible for LL and is randomised between HP and PA.

LL: the abdominal cavity is irrigated with six litres of warm saline. At the end of the procedure a Douglas drain is inserted via the right lateral port.

HP: The perforated diseased part must be resected. There is no need of having the distal transsection line on the proximal rectum. An end-colostomy is performed according to the preference of the operating surgeon, the same accounts for closing the rectal stump.

PA: Sigmoidectomy is done according to the guidelines of the American Society of Colon and Rectal Surgeons[26,27]. The distal transsection margin has to be on the proximal rectum, the proximal margin is determined by the absence of wall thickening due to diverticulitis. The type of anastomosis and the decision to perform a defunctioning loop-ileostomy are to the discretion of the surgeon on call.

Leaving a Douglas drain after resectional surgery is at the discretion of the operating surgeon. The resected tissue is sent for histological investigation to exclude malignancy.

Antibiotics are administered for seven days in both groups. Postoperatively, oral diet and mobilisation are advanced as soon as possible. Within four to six weeks after surgery a sigmoidoscopy is performed to exclude malignancy as the underlying cause of the perforation.

After the sigmoidoscopy is performed, the patient will be offered reversal of the stoma, when he or she is found eligible for surgery by the surgeon and anaesthesiologist.

### Statistical analysis

The analysis will be performed in accordance with the intention to treat principle.

In the LOLA-arm of the study, the assumpted difference in the combined number of mortality and major morbidity between laparoscopic lavage and resection is 15%. With a two sided likelihood ratio test and a significance level of 0.05, a sample size of 132:66:66 will be necessary to detect this difference. With a group size of a hundred patients per arm it is also possible to find a significant difference (alpha = 0.05, beta = 0.1) of at least 10% in subscales of the SF-36, a validated quality of life questionnaire, at two, four, thirteen, 26 and 52 weeks after initial surgery.

In the DIVA-arm 212 patients are needed to significantly demonstrate a difference in stoma free survival between both treatment arms, using log rank statistics with a power of 90% and a type I error of 5%. The suspected postoperative mortality for HP and PA is equally high (+ 15%)[8]. About 60% of the patients that underwent HP have their stoma reversed[11,12]. When corrected for the expected mortality before reversal, the reversal rate will be 50%. Patients with a protective loop-ileostomy after PA will have their enterostomy reversed in over 85%[12]. After correction for expected mortality before reversal, this will result in a 72% stoma reversal rate in the initial patient population.

### Economic evaluation

Comparisons of the different surgical strategies in the economic evaluation will be analogous to the analyses of the clinical endpoints. The economic evaluation will be performed from a societal perspective, with the costs per unit improvement on the primary clinical endpoints, defined as combined mortality and morbidity for the LOLA-arm, and stoma free survival for the DIVA-arm.

We hypothesise that a more effective intervention will be associated with less health care utilisation as well as absence from paid work (productivity costs). Therefore, the primary analysis will be a cost-effectiveness analysis that evaluates costs associated with an improved surgical outcome.

In addition, a secondary analysis will evaluate cost differences in relation to differences in quality-adjusted life-years (QALYs). This cost-utility analysis, resulting in an incremental cost-effectiveness ratio expressed in costs per QALY, will be included to allow comparison with other health-related interventions or programs. With a study horizon of twelve months, no discounting will be applied. We will differentiate between direct medical, direct non-medical and indirect costs.

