**Methods/Design:**

In this multicentre randomised trial all patients with perforated diverticulitis are included. Upon laparoscopy, patients with purulent peritonitis are treated with laparoscopic lavage and drainage, Hartmann's procedure or sigmoidectomy with primary anastomosis in a ratio of 2:1:1 (LOLA-arm). Patients with faecal peritonitis will be randomised 1:1 between Hartmann's procedure and resection with primary anastomosis (DIVA-arm). The primary combined endpoint of the LOLA-arm is major morbidity and mortality. A sample size of 132:66:66 patients will be able to detect a difference in the primary endpoint from 25% in resectional groups compared to 10% in the laparoscopic lavage group (two sided alpha = 5%, power = 90%). Endpoint of the DIVA-arm is stoma free survival one year after initial surgery. In this arm 212 patients are needed to significantly demonstrate a difference of 30% (log rank test two sided alpha = 5% and power = 90%) in favour of the patients with resection with primary anastomosis. Secondary endpoints for both arms are the number of days alive and outside the hospital, health related quality of life, health care utilisation and associated costs.

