## Background

Diverticular disease is an important condition in terms of healthcare utilisation and it is one of the five most costly gastrointestinal disorders in westernised countries[1]. Despite this high prevalence, treatment of all different stages of diverticular disease is still hardly evidence based, hence containing a lot of controversies.

Perforated diverticulitis is a perforation of an inflamed diverticulum of the large bowel, mostly the sigmoid, resulting in either purulent or faecal peritonitis (Hinchey stadia III or IV). Both conditions require emergency surgery[2,3]. Regardless of selected strategy emergency operations for acute perforated diverticulitis are associated with substantial morbidity (up to 50%) and mortality (15 to 25%)[3-8]. Primary sigmoidectomy with or without anastomosis has become the standard practice for patients with generalised peritonitis complicating diverticulitis [6-10] and for many surgeons the Hartmann's procedure remains the favoured option. Restoration of bowel continuity after this procedure is a technically difficult operation, with high morbidity and mortality rates[11,12]. Therefore stoma reversal after HP is only performed in 50 to 60% of the patients, thereby compromising quality of life and increasing costs[13,14].

Recently laparoscopic lavage (LL) emerged as an effective alternative for patients with perforated diverticulitis with purulent peritonitis[15]. This nonresectional procedure has first been described by O'Sullivan in 1996[16]. In 2009, a systematic review on all studies on laparoscopic lavage with a total number of 231 patients was performed. Mortality was less than 2% and a (permanent) colostoma was avoided in the majority of these patients[15-22]. So laparoscopic lavage for perforated purulent diverticulitis has a great potential in improving health and reducing costs.

Nevertheless, since sigmoidectomy is still considered the standard of care for perforated diverticulitis, implementation of LL might be variable. Some surgeons will embrace lavage because of its technical simplicity; other might be reluctant fearing failure of this novel strategy. Only a head to head comparison of both surgical strategies will provide an evidence based surgical approach of patients with perforated diverticulitis with purulent peritonitis (LOLA-arm).

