### Study objectives

For this two-armed randomised trial two objectives can be defined to determine the optimal strategy for the treatment of perforated diverticulitis. First, is laparoscopic lavage for patients with purulent peritonitis superior compared to sigmoidectomy, in terms of mortality, morbidity, quality of life, health care utilisation and associated costs (LOLA-arm)? Secondly, is HP or PA the superior approach for patients with purulent or faecal generalised peritonitis in terms of stoma free survival, quality of life and cost-effectiveness (DIVA-arm)?

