**Figure 1 F1:**
[figure not shown]
**Study profile**.

In case of purulent peritonitis (Hinchey III) patients are randomised to LL, HP or PA (LOLA-arm). The best evidence indicates that the latter two resectional strategies are equal in terms of postoperative morbidity and mortality in case of generalised peritonitis[8]. For this reason a three way 2:1:1 randomisation is performed. In case of an overt perforation with faecal peritonitis (Hinchey IV) patients will undergo laparotomy and are randomised 1:1 to either undergo HP or PA.

Patients who are either ineligible for trial entry, who show other causes of peritonitis than diverticulitis at laparoscopy or who do not wish to take part in the study are treated at the discretion of the surgeon on call. These patients will be registrated by the trial coordinator.

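### The LOLA economic evaluation compares lavage only with Hartmann's procedure and primary anastomosis pooled; a three-strategy comparison in purulent peritonitis should be added

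*Protocol article*

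**What the plan says.** All references are to the protocol article.

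- Economic evaluation sets one rule for both arms: "Comparisons of the different surgical strategies in the economic evaluation will be analogous to the analyses of the clinical endpoints". For LOLA the primary economic result is cost per unit improvement in combined mortality and morbidity; for DIVA it is cost per unit of stoma free survival. Cost per QALY is secondary.
- Statistical analysis gives a single LOLA contrast: "the assumpted difference in the combined number of mortality and major morbidity between laparoscopic lavage and resection is 15" per cent. The size follows from it: "a sample size of 132:66:66 will be necessary to detect this difference".
- Study objectives puts the LOLA cost question against one comparator; it asks about "laparoscopic lavage for patients with purulent peritonitis superior compared to sigmoidectomy, in terms of mortality, morbidity, quality of life, health care utilisation and associated costs".
- The text under Figure 1 explains the 2:1:1 allocation by HP and PA being "equal in terms of postoperative morbidity and mortality in case of generalised peritonitis".
- Background says that only 50 to 60% of stomas are reversed after HP, "thereby compromising quality of life and increasing costs". Statistical analysis plans on reversal in 50% after HP and 72% after PA, both corrected for mortality.
- HP and PA have their own economic comparison in DIVA. Study objectives defines it for purulent or faecal peritonitis.

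**The concern.** Pooling HP and PA for the clinical endpoint rests on their assumed equality on that endpoint. The economic rule carries the same grouping over to costs and QALYs, where the article itself gives reasons to expect a difference.

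A cost-effectiveness comparison should help a surgeon or payer choose between procedures. In purulent peritonitis the choices are lavage, HP and PA. A comparator that is half HP and half PA gets its weights from the randomisation ratio, and the article states no practice mix to match them. If one resection is better value than the other, the mix is an easier comparator for lavage than the better resection. A favourable result against the mix would then not show that lavage is the best-value option.

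**Working it through.** **1. Is the LOLA contrast pooled?** Inputs: 25% v 10%, two-sided alpha 5%, power 90% (Abstract); likelihood ratio test and 132:66:66 (Statistical analysis).

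- Likelihood ratio test, n = 132 per group: noncentrality = 2n[l(0.25; 0.25) + l(0.10; 0.10) - l(0.25; 0.175) - l(0.10; 0.175)], with l(p; q) = p ln q + (1 - p) ln(1 - q). This gives 10.57 and power 90.2%. Exact enumeration gives 90.7%.
- Normal approximation: 133 per group needed; 132 v 132 has 89.8% power.
- Lavage against one resection only, 132 v 66: 77.3% power (normal approximation).

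The stated size is reproduced for 132 v 132 and not for 132 v 66. The LOLA contrast is therefore lavage v pooled resection, with HP weight 66/132 = 0.5.

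**2. What does the mix do to the economic contrast?** For mean cost or mean QALYs, mix = (HP + PA)/2, so

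lavage - mix = (lavage - PA) - 0.5 x (HP - PA).

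Write NMB for net monetary benefit, suppose PA is the better-value resection, and let d = NMB(PA) - NMB(HP) > 0. Then NMB(mix) = NMB(PA) - d/2. Lavage beats the mix but is worse value than PA whenever

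NMB(PA) - d/2 < NMB(lavage) < NMB(PA).

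The window has width d/2 and closes only if d = 0. The same holds with HP and PA exchanged.

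**3. How large could the QALY part be?** The documents give reversal rates but no reversal times or utilities, so this is an illustration. Assumptions: reversal at the same day T in both groups, the same number and timing of deaths, every resected patient starting with a stoma, and utility loss u while a stoma is present.

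- Stoma-day gap, HP minus PA, in year one = (0.72 - 0.50) x (365 - T).
- T = 0 (upper bound): 0.22 x 365 = 80 days. T = 120: 0.22 x 245 = 54 days.
- QALY gap at u = 0.10: 80/365 x 0.10 = 0.022; 54/365 x 0.10 = 0.015.
- Half of that is the shift in the lavage contrast relative to PA: 0.011 and 0.007.

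The shift is proportional to u: 0.110u at T = 0 and 0.074u at T = 120. Halving or doubling u halves or doubles it. Study outline leaves the loop-ileostomy to the surgeon; PA patients without one would widen the gap, by an amount the article does not allow to be calculated.

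**4. And the cost part?** It is half the HP - PA cost difference, for which no figure is given. Background suggests higher costs after HP through non-reversal. Against that, more reversals after PA mean more reversal operations within the twelve-month horizon. The sign is not settled by the documents.

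**5. What does separating the strategies cost in precision?** With equal standard deviations, the standard error for 132 v 66 relative to 132 v 132 is sqrt(1/132 + 1/66) / sqrt(2/132) = sqrt(1.5) = 1.22. For HP v PA within LOLA (66 v 66) the ratio is sqrt(2) = 1.41.

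**The case against.** The strongest reply is that DIVA already compares HP and PA economically, with purulent patients included, and that the identity in step 2 needs only the HP - PA difference to move from lavage v mix to lavage v PA. This stands in part: a reader might infer that the two resections are never compared on value, and that is not so. But DIVA mixes purulent and faecal disease, so its HP - PA difference need not be the one in purulent patients. Its primary economic result is also in another effect unit than LOLA's. Cost per QALY shares a unit across the arms, but the article plans no comparison of lavage with each resection.

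Second, Economic evaluation is a short section of a journal article. It does not use the word pooled and does not rule out a three-way analysis, and ranking and bootstrap details belong in a fuller document. That is fair for the details. The choice of contrast, however, is stated here.

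Third, the Discussion says that Dutch standard care is either HP or PA, so lavage against mixed resection is a legitimate question, and it is the one in Study objectives. This stands, and is why the pooled contrast should remain. Background says many surgeons favour HP; if PA were the better value, an HP-heavy practice mix would be an even easier comparator than 50:50.

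Fourth, LOLA's primary economic effect measure is one on which HP and PA are assumed equal. This also stands: on the effect side the problem lies mainly in the secondary cost-per-QALY analysis. The cost side is affected in both.

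**Conclusion.** The point holds in a limited form. The LOLA economic contrast inherits a pooling whose stated justification covers postoperative morbidity and mortality only. Lavage can therefore look good value against the mix while one resection is better value, within a window of half the HP - PA difference in net monetary benefit.

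The size of that window is unknown. The QALY part is small, about 0.007 to 0.011 against PA, and rests on the assumptions in step 3, above all equal reversal timing and a utility loss of 0.10. The cost part has no established size or sign.

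Three stronger readings are tempting and not supported:

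- That the planned analysis will favour the wrong procedure. This needs lavage to fall inside the window, and the documents give no costs or QALYs from which to tell.
- That the error always flatters lavage relative to PA. This needs HP to be worse value than PA, which the article suggests qualitatively but does not quantify.
- That the stoma-day gap exceeds 80 days because HP stomas are reversed later. The article gives no reversal times by procedure; Study outline offers reversal after sigmoidoscopy without distinguishing them.

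Nothing here affects the clinical primary comparison.

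**What to change.** In Economic evaluation, keep lavage v pooled resection as the comparison that answers the LOLA question in Study objectives, and add wording such as:

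*In patients with purulent peritonitis, lavage, HP and PA will also be compared as three separate strategies in an incremental analysis (removal of dominated strategies, or net monetary benefit), with bootstrap uncertainty. A conclusion on the cost-effectiveness of lavage will be drawn against each resection and not from the pooled contrast alone.*

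The cost is extra analysis work and wider intervals, with standard errors about 1.22 times larger for lavage against each resection. No change in allocation, sample size or data collection is needed: the three groups are randomised separately, and EQ-5D and health care use are already recorded. The added analysis is estimation, so the lower power of 132 v 66 on the clinical endpoint is no reason to enlarge the trial.

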### Data collection and monitoring

An electronic Case Report Form (CRF) will include general patients data: sex, age, medical history, POSSUM-score, preoperative APACHE-score, surgical parameters, Hinchey score, data concerning type of intervention, complications, mortality, duration of hospital and intensive care stay and the patients response to the questionnaires.

Patients will be followed for a period of twelve months. During this follow-up period patients will complete a set of questionnaires (SF-36, EQ-5D and GIQLI) two, four, thirteen, 26 and 52 weeks after the initial surgery. The questionnaires will be sent to the patients by mail accompanied by a stamped return envelope. Collection of the questionnaires will be safeguarded by the trial coordinator.

At four, thirteen, 26, 39 and 52 weeks after initial surgery, the patients will be asked to complete questionnaires to assess complications, additional interventions, readmissions, duration of hospital and intensive care stay, visits to the outpatient clinic, number of days of sick leave and to ensure completions of the questionnaires.

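### EQ-5D is not measured between weeks 26 and 52, half the QALY horizon, although patients already complete a questionnaire at week 39 (minor)

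*Protocol article*

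**What the plan says.** Under Data collection and monitoring, the Protocol article fixes the quality-of-life schedule: "patients will complete a set of questionnaires (SF-36, EQ-5D and GIQLI) two, four, thirteen, 26 and 52 weeks after the initial surgery". The same section sets a second schedule for events and resource use: "At four, thirteen, 26, 39 and 52 weeks after initial surgery, the patients will be asked to complete questionnaires to assess complications, additional interventions, readmissions", and so on to sick leave. The two schedules differ in that week 2 appears only in the first and week 39 only in the second.

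Under Economic evaluation, the main analysis is cost-effectiveness against the primary clinical endpoints. Beyond that, "a secondary analysis will evaluate cost differences in relation to differences in quality-adjusted life-years (QALYs". The horizon is one year: "With a study horizon of twelve months, no discounting will be applied". The article does not say how utilities are joined between measurements.

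Under Study outline, a sigmoidoscopy is done four to six weeks after surgery, and then "After the sigmoidoscopy is performed, the patient will be offered reversal of the stoma", subject to fitness for surgery. No latest or expected reversal date is given.

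**The concern.** A QALY over twelve months is the area under the utility curve. The interval from week 26 to week 52 is half of that year, and it rests on its two end values alone. Stoma reversal, its complications and the later gain in health can all fall inside it, since reversal is offered after the sigmoidoscopy with no end date.

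The Statistical analysis section expects different shares of patients to be reversed after HP and after PA. The Background describes restoring continuity after HP as difficult and as carrying high morbidity. The groups could therefore also differ in when reversal takes place and in how well it goes. If they do, and the area is drawn with straight lines, part of the QALY difference between them would be lost or distorted, and the cost per QALY with it. An analysis plan can choose how to interpolate, but it cannot supply a measurement that was not taken. The week-39 contact, at the midpoint of the gap, already exists.

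**Working it through.** The article gives no QALY figure or QALY precision, so there is none to reproduce. The check is of the schedule itself.

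**Inputs from the article**
- EQ-5D at weeks 2, 4, 13, 26 and 52; horizon 52 weeks (Data collection and monitoring; Economic evaluation).
- Share of all patients reversed: HP 50%, PA 72% (Statistical analysis).

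**Assumptions, not in the article**
- Linear interpolation between measurements.
- Utility rises by d in one step at reversal week t. Central d = 0.10, range 0.05 to 0.20.
- Reversal weeks as stated in each scenario.

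**Step 1. Share of the horizon in each interval.** 0–2: 2/52 = 3.8%. 2–4: 2/52 = 3.8%. 4–13: 9/52 = 17.3%. 13–26: 13/52 = 25%. 26–52: 26/52 = 50%.

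**Step 2. Error for one patient reversed in weeks 26–52, as planned.**
- Credited: d × (26/2)/52 = 0.25d, for every t.
- True: d(52−t)/52.
- Error: 0.25d − d(52−t)/52. This is zero at t = 39, close to −0.25d just after week 26, and +0.25d at week 52.
- If reversals are spread evenly over the interval, the mean error is zero.

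**Step 3. The same patient with a week-39 value.**
- Reversed in weeks 26–39: credited (6.5 + 13)/52 = 0.375d.
- Reversed in weeks 39–52: credited 6.5/52 = 0.125d.
- Largest error: ±0.125d.

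| d | Largest error, as planned | With week 39 |
|---|---|---|
| 0.05 | 0.0125 | 0.006 |
| 0.10 | 0.025 | 0.0125 |
| 0.20 | 0.050 | 0.025 |

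A reversal in weeks 13–26 carries an error of at most ±0.125d in either case. The change does not affect it.

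**Step 4. Arm level, d = 0.10, all HP reversals at week 45 and all PA reversals at week 30.**
- As planned, HP: 0.025 − 0.10 × 7/52 = +0.0115; × 0.50 = +0.0058.
- As planned, PA: 0.025 − 0.10 × 22/52 = −0.0173; × 0.72 = −0.0125.
- PA minus HP: −0.0182.
- With week 39, HP: 0.0125 − 0.0135 = −0.0010; × 0.50 = −0.0005.
- With week 39, PA: 0.0375 − 0.0423 = −0.0048; × 0.72 = −0.0035.
- PA minus HP: −0.0030.

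Over d = 0.05 to 0.20, the planned bias runs from −0.009 to −0.036 and the bias with week 39 from −0.0015 to −0.006.

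**Step 5. Other timings, d = 0.10.**

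| HP week | PA week | Bias as planned | With week 39 |
|---|---|---|---|
| 52 | just after 26 (outer bound) | −0.031 | −0.015 |
| 45 | 30 | −0.018 | −0.003 |
| 39 | 30 | −0.0125 | −0.010 |
| 40 | 14 | −0.009 | −0.002 |
| 36 | 20 | +0.004 | −0.003 |

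Every row puts all of an arm's reversals at one week. In the first three rows they all fall in the gap. If only half of each arm's reversals fell there, at the same weeks, the −0.018 in the second row would halve to about −0.009.

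**The case against.** **The straight line is an assumption.** The article names no interpolation method, and a condensed article may leave it to the full plan. A reader might infer that half of every patient's QALY is fixed as a straight line. The document does not support that: the method is open, deaths within the year would not be handled this way, and the timing error touches only patients whose health changes in weeks 26–52. This objection stands and limits the point.

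**Reversal dates should be known.** Stoma free survival is analysed by log-rank test, and the week-39 and week-52 forms ask about additional interventions. An analyst could switch from the week-26 to the week-52 utility at the reversal date, and in the step model above that gives the exact area. This stands in part. It replaces a measurement with an assumed shape and cannot show a temporary loss around surgery or any other change in the interval. In fairness, a single value at week 39 would often miss a short dip as well.

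**Error is not bias.** A reader might infer that the HP v PA or lavage v resection result is biased because the groups differ in how many patients have a stoma to reverse. That does not follow. The mean error is zero when reversals are evenly spread over the gap, and bias needs timing within it to differ between groups. The article gives no reversal times.

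**Two further inferences fail.** The plan does not treat reversal timing as worthless: even with straight lines, a reversal in weeks 13–26 earns (6.5 + 26)/52 = 0.625d against 0.25d in weeks 26–52. Nor does dating costs to week 39 create a mismatch with the health effect, because costs are totalled over the year without discounting. It would also mislead to set the largest per-patient error beside an arm-mean gain such as 22 points times d, since these are different quantities.

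**The week-39 value does not always help.** It cannot separate two reversals on the same side of week 39, such as weeks 28 and 37, and in the 39 v 30 scenario it removes little of the bias.

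**Conclusion.** The point holds as a minor, inexpensive improvement to a secondary analysis. It is not an error or a contradiction in the plan. Half of the twelve-month QALY horizon has no utility value between its end points, and this cannot be repaired after the trial. Under linear interpolation, the date of a reversal within weeks 26–52 makes no difference to the QALY, with an error of up to ±0.25d per affected patient.

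Whether this biases the HP v PA comparison depends on three things that the article does not give: the utility gain, the share of reversals falling after week 26, and how their timing differs between arms. The illustrative −0.018 QALY rests on d = 0.10, on all reversals falling in the gap, and on PA being reversed 15 weeks earlier than HP. Other timings give smaller biases, larger ones, or one of opposite sign. The primary endpoints and the primary cost-effectiveness analysis are unaffected.

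**What to change.** Add EQ-5D to the existing week-39 questionnaire, so that it is taken at weeks 2, 4, 13, 26, 39 and 52, and use the week-39 value in the QALY area. The longest interval falls from 26 to 13 weeks, and the largest interpolation error for reversals in weeks 26–52 falls from 0.25d to 0.125d.

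The cost is one short instrument on a form patients already receive, slightly more patient burden and data entry, and a minor amendment. No extra visit is needed.
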